#### Secondary variables

Secondary variables are the European Quality of Life-5 Dimensions (EQ-5D; with a range from approximately − 0.5 to 1, with higher scores indicating better quality of life) using the Swedish translation [43, 44].

Numeric rating scales (NRS) are used to assess arm and neck pain. The scales range from 0 to 10, 0 being the best and 10 the worst. MCID for NRS neck and arm is not yet determined [45].

#### Tertiary variables

Tertiary variables, complications, and reoperations will be collected as they may occur.

#### Radiology

The following radiological examinations will be performed: X-ray radiograph in flexion/extension of cervical spine, and MRI and CT scan will be carried out preoperatively and after 1 and 2 years. In order to evaluate the degree of decompression, a postoperative CT will also be performed. The degree of restenosis over time, development of adjacent segment pathology, facet joint degeneration, range of motion changes, and fusion healing will be evaluated.

### Participant timeline {13}

Patient are randomized and enrolled in the study at the consultation with spine surgeon; there is usually 4–18 weeks waiting before surgery. During this time, BASELINE data is collected. After intervention, CT scan is performed then the patients are followed with PROMS and radiological studies after 4–6 weeks, 3 months, 1 year, and 2 years.

**Table Tabb:** 

OMSAP	Study period					
	Enrolment	Surgery	Post-allocation			
**Timepoint**	***− 4–18 weeks***	**0**	***4–6 weeks***	***3 months***	***1 year***	***2 years***
**Enrolment:**						
**Eligibility screen**	X					
**Informed consent**	X					
**Allocation**	X					
**Interventions:**						
***[ACDF OR PF]***		X				
**Assessments:**						
***[MRI, CT, Flex/Ext-X-ray]***	X				X	X
***[NDI, NRS, EQ-5D]***	X		X	X	X	X
***[Post Op. CT]***		X				

### Sample size {14}

The MCID in the NDI is approximately 15% [50], and the standard deviation (SD) in the NDI is 25%. With these parameters, a two-sided superiority trial with significance level at 0.05 and power at 80% will require 44 patients in each group. To make up for crossovers, noncompliance, and follow-up losses, the total number of patients is set at 110.

### Recruitment {15}

Participating centers, Örebro University Hospital (primary site), Uppsala University Hospital, Umeå University Hospital, and Ryggkirurgiskt Centrum Stockholm have been chosen for their high volume of cervical cases with cervical radiculopathy. These patients are generally referred by a general practitioner and are eligible for consultation with a consultant spine surgeon. To achieve a fast and easy enrollment, a web-based software, Smart-Trials, is used to register consent, inclusion, and randomization. A written consent is also given during the consultation with spine surgeon.

## Assignment of interventions: allocation

### Sequence generation {16a}

Randomization is achieved by registering the patient in Smart-Trials software (www.smart-trial.com), which will generate allocation to either ACDF or PF. It is not possible to change group after randomization.

### Concealment mechanism {16b}

Concealment mechanism is provided by the software, which allows the user to preform randomization without the possibility of knowing the outcome beforehand.

### Implementation {16c}

Each spine surgeon has individual logging, and the log-on process is with a two-stage verification using logging and mobile phone SMS code. The spine surgeon implements the allocation.

## Assignment of interventions: blinding

### Who will be blinded {17a}

Blinding is not possible; the interventions are different and neither the patient nor the surgeon are blinded. X-ray assessment is not possible to blind.

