### Data collection and management

#### Plans for assessment and collection of outcomes {18a}

The Swedish Spine Register [52] is used for gathering data. Patient-reported outcome measures (PROMs; NDI and EQ5-D [48–50]) are sent to the patient by mail at 1 and 2 years of follow-up. PROMs for the 4–6 weeks and 3 months follow-up are not standard to the SweSpine protocol which is why these are mailed separately to the patients. The MRI, CT, and flexion-and-extension radiographs are assessed by 2 spine surgeons independently. In case of non-consensus, a discussion will be performed until consensus is reached. Standard protocols for MRI cervical spine and CT cervical spine are used.

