The cost-risk benefit for ACDF vs. PF needs to be considered; the approach-related complications and reoperations rates are important from financial perspective. ACDF have more implications than PF due to the anatomical facts of an anterior approach; this is in favor for PF. Implants are not utilized for PF; this lowers the coast of surgery in favor for PF. Surgical selection bias is a factor that must be considered when looking at retrospective studies of ACDF vs. PF. The difference in various clinical settings may influence the choice of method as factors such as multilevel vs. single level surgery, smoking vs. non-smoking, and prior instability on dynamic radiographs. The most decisive difference between ACDF and PF is the fusion at the index level. In previous studies on cervical radiculopathy, motion preservation using artificial disks seem to decrease the incidence of radiological adjacent segment pathology (RASP) next to a fused segment. But when it comes to clinically relevant adjacent level pathology (CASP), especially if leading to surgery, the data is less compelling with a 7.1–8.5% reoperations rate in ACDF for CASP [56, 57]. Our study design, with X-ray, MRI, and CT at regular intervals, will allow us to shed some additional light on the unsettled issue if lost or maintained motion at the index segment and will protect from CASP in the long-term.

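### Blinding is ruled out for all image reading, but only post-operative index-level reads necessarily reveal the arm; pre-operative scans can be masked fully and adjacent levels in part

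*Protocol article*

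**What the plan says.** Under Who will be blinded {17a}, the protocol article says that "neither the patient nor the surgeon are blinded" and that "X-ray assessment is not possible to blind". The entry under Procedure for unblinding if needed {17b} confirms that there is no blinding in the trial.

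Plans for assessment and collection of outcomes {18a} sets the reading rule: "The MRI, CT, and flexion-and-extension radiographs are assessed by 2 spine surgeons independently". It continues: "In case of non-consensus, a discussion will be performed until consensus is reached". No masking to arm, identity or visit is described.

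Under Radiology, the schedule is that "MRI and CT scan will be carried out preoperatively and after 1 and 2 years", with one further CT after surgery. The targets are listed there: "The degree of restenosis over time, development of adjacent segment pathology, facet joint degeneration, range of motion changes, and fusion healing will be evaluated". The Discussion gives these images a purpose. It says "Our study design, with X-ray, MRI, and CT at regular intervals, will allow us to shed some additional light" on whether keeping or losing motion at the operated segment affects adjacent-level pathology.

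**The concern.** The statement makes no distinction by level or by time point. What reveals the arm on an image is the surgery itself, so the claim can only be as wide as the surgery is visible. Before the operation nothing is visible. At the neighbouring levels after the operation, the finding being graded lies outside the segment that was treated.

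Adjacent degeneration and facet degeneration are graded by judgement. If both readers know the arm, their grades can shift together. Two independent reads reduce each reader's random error but do not remove a shift that both share, and neither does discussion to consensus. The pre-operative grade matters too, because it is the starting point from which new adjacent pathology is judged. A baseline graded with knowledge of the arm carries that knowledge into the change score.

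At stake is the comparison of adjacent-segment change, which the Discussion presents as something the trial's imaging will inform.

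**Working it through.** No figure in the protocol measures reader bias, and the sample size concerns NDI, so there is no planned number to reproduce. The check sets the sections side by side and asks, read by read, whether the image shows the arm.

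**1. Scope of the statement.** Section {17a} speaks of X-ray assessment. That MRI and CT are also read open follows from {17b}, which allows no blinding, together with {18a}, which describes unmasked reading of all three modalities. Confidentiality {27} mentions de-identification for PROM data only, so it does not supply masking of images.

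**2. What the surgery leaves on the image.** The ACDF description includes a spacer and a plate with screws, or a cage with integrated screws. The PF description includes removal of the medial third of the facet joint and mentions no implant. Either is a visible sign at the operated segment.

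**3. Read by read.**

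| Read | Does the image show the arm? | Can it be masked? |
|---|---|---|
| Pre-operative MRI, CT, flexion/extension | No, surgery has not happened | Yes |
| Post-operative CT, decompression | Yes, implant or facet resection | No |
| 1 and 2 years, index level: restenosis, fusion healing, motion, facet joint | Yes | No |
| 1 and 2 years, adjacent-level degeneration | Only through what shows from the index level | In part |

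**4. Pre-operative scans and knowledge of allocation.** Participant timeline {13} places randomization at the consultation, with baseline data collected during the 4 to 18 weeks before surgery. Allocation can therefore be known when baseline scans are made. The protocol does not say when they are graded. Hiding identity and allocation from the reader settles the matter whatever the timing.

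**5. Adjacent levels.** The plate is screwed to the vertebrae on either side of the operated disk, and each of these also borders an adjacent disk. A tight crop cuts into the segment to be graded, while a wider one shows hardware. Covering the index level therefore masks some reads and not others. That it can be done at all is a methodological judgement; the documents do not address it.

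**6. Can the protocol's rates size the bias?** Background and rationale {6a} gives 10-year adjacent segment disease of 25.6% after ACDF and 6.7% after PF. Under an assumed constant hazard, the 2-year values are:

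- ACDF: 1 − (1 − 0.256)^(2/10) = 5.7%, times 55 = 3.2 patients
- PF: 1 − (1 − 0.067)^(2/10) = 1.4%, times 55 = 0.8 patients

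The difference is about 2.4 patients. This is correct arithmetic on another endpoint. The rates are for adjacent segment disease, whereas the reads at issue are radiological grades, and the Discussion itself separates radiological from clinical adjacent pathology. The calculation also assumes that all 55 per arm are imaged, although the sample size section allows for losses. It does not size the bias.

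**The case against.** The strongest reply is that little depends on these reads. Radiology has its own heading and is not among the named primary, secondary or tertiary variables. The primary outcome is a patient questionnaire that no image reader can influence. The Limitation section concedes that adjacent disease and restenosis need longer follow-up than two years. This stands, and it limits the weight of the point. It does not make the blanket statement right.

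A second reply is that the statement is largely true and masking of adjacent levels is doubtful because of the plate. This stands in part: masking will be incomplete in ACDF cases. It has no bearing on pre-operative scans, where nothing prevents masking.

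Three stronger readings are tempting and are not supported:

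- **That the reads will be biased against ACDF.** The background reports fusion as a suspected cause of adjacent degeneration, but calls the cause disputed and allows for ordinary ageing. The Discussion voices an expectation against PF, namely continuing degeneration and a rising risk of restenosis. The expectations run both ways, so no direction can be stated.
- **That two or three differently graded patients would equal the whole expected effect.** As shown in the working, this carries disease rates over to a radiological grade.
- **That surgeons will read their own patients, or that separate grades are lost at consensus.** The article is silent on both. A condensed article commonly leaves reader assignment and record keeping to the full protocol, so silence is no finding.

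**Conclusion.** The point holds in limited form. The protocol takes an affirmative position that image assessment cannot be blinded, and that position is justified only for post-operative index-level reads. Pre-operative scans can be read without knowledge of arm, and adjacent-level reads can be masked in part. As written, the plan leaves the radiological comparison of adjacent-segment change open to avoidable reader bias of unknown size and direction.

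The NDI result, the sample size and the other patient-reported outcomes are untouched. This is a cheap improvement to a supporting comparison, not a threat to the trial's main conclusion. It rests on two assumptions: that {17b} and {18a} extend open reading to MRI and CT, and that covering the index level leaves enough of the adjacent segment to grade in a useful share of cases.

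**What to change.** In Who will be blinded {17a}, limit the statement to post-operative reads of the index level: decompression, restenosis, fusion healing and index-level motion.

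In Plans for assessment and collection of outcomes {18a}, add that the same two readers will:

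- grade pre-operative scans de-identified and without knowledge of allocation;
- grade adjacent levels with identity masked and the index level covered where feasible, in a session separate from the index-level reads.

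Report index-level reads as unblinded, together with any adjacent-level read in which hardware or artefact revealed the arm.

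The cost is relabelling and cropping of images that Data management {19} says are already stored digitally, plus a separate reading session. No new scan or reader is needed. The downside is incomplete masking in ACDF cases, because plate, screws or artefact lie next to the adjacent disks.

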### Procedure for unblinding if needed {17b}

No blinding

### Data collection and management

#### Plans for assessment and collection of outcomes {18a}

The Swedish Spine Register [52] is used for gathering data. Patient-reported outcome measures (PROMs; NDI and EQ5-D [48–50]) are sent to the patient by mail at 1 and 2 years of follow-up. PROMs for the 4–6 weeks and 3 months follow-up are not standard to the SweSpine protocol which is why these are mailed separately to the patients. The MRI, CT, and flexion-and-extension radiographs are assessed by 2 spine surgeons independently. In case of non-consensus, a discussion will be performed until consensus is reached. Standard protocols for MRI cervical spine and CT cervical spine are used.

#### Plans to promote participant retention and complete follow-up {18b}

Patients that do not reply on the first set of PROMs will get two reminders by mail. If still no response, they will be approached once by telephone, after which they will be excluded. Patients that choose to opt out will be excluded upon their request. Outcome PROMs and radiology will be collected for the time they remained in the study, unless the patient demands that this data is removed.

### Data management {19}

The primary site is where all the study data will be stored in a protected database; sources of collected data are radiology outcomes and PROMS. Radiology outcomes are collected from all the sites and stored digitally on secure drive with backup provided by the Department of Radiology, secured by 1-stage verification login.

PROMS outcome are collected by two different pathways: first is by SweSpine for 1- and 2-year data and by the primary site for 4–6 weeks and 3 months data. SweSpine data are accessible by one-stage verification login on the SweSpine main page. SweSpine data can be viewed by the spine surgeons with the patient’s ID. This data can only be accessed for study purpose and with Swedish Ethical Review Authority’s approval. Upon retrieval of 1 and 2 years data by the investigator, this is then stored on a hard drive with backup and 1-stage verification login.

PROMS for 4–6 weeks and 3 months are manually collected and converted to digital form by the primary site by the controller and investigator. All PROMS data are checked by the controller and investigator before analysis. All PROM data will be processed by using IBM SPSS statistics or other equivalents by the investigator with support of a statistician; also, this data will be password protected.

Data from Smart-Trials is not used as outcome measures and is stored upon completion in a database accessible only by the primary investigator.

### Confidentiality {27}

All data management and analysis are done using unidentified PROMS data; only the investigator team has access to the ID of the recruited participants. Trial data will not be shared with other researchers.

### Plans for collection, laboratory evaluation, and storage of biological specimens for genetic or molecular analysis in this trial/future use {33}

No laboratory test or biological materials are collected during this trial.

### Interim analyses {21b}

An interim analysis will be performed by an independent observer when 40 patients are included, regarding NDI difference and adverse effect [53]. If severe adverse events are noted, the attending spine surgeon will contact the investigator of the study.

### Methods for additional analyses (e.g., subgroup analyses) {20b}

No primary subgroup analyses are planned.

### Methods in analysis to handle protocol non-adherence and any statistical methods to handle missing data {20c}

Missing data will be imputed using multiple imputation [54].

### Plans to give access to the full protocol, participant level-data, and statistical code {31c}

No later than 3 years after the collection of the 2-year data after the randomization PROMS, we will deliver a completely deidentified dataset if requested.

### Composition of the data monitoring committee, its role and reporting structure {21a}

Data monitoring is performed on a weekly basis by the main coordinator and controller with support of the local coordinator; this is to ensure that all the events, i.e., PROMS, radiology, is performed according to protocol. Data monitoring committee comprises of:

Principal investigator: [name] MD. Responsible for recruitment, data collection, adherence to study protocol

Main coordinator and controller: [name], responsible for PROMS, radiology

Interim analysis is also performed after the 40 participants have been included and surgical intervention is performed, by the independent observer.

Independent observer: Associate [name] MD. PhD

### Adverse event reporting and harms {22}

Adverse events (AE) that are anticipated are infection, implant failure, neurologic impairment post-surgery, and other rare approach-related complications like esophagus perforation and nerve injury. AE are reported by the senior spine surgeon that performed the surgical intervention to the primary investigator.

Serious adverse events (SAE) are not anticipated; they are reported by the senior spine surgeon according to the Swedish healthcare standards which depend on the type of SAE. Such SAE may include deep vein thrombosis with pulmonary embolism and subsequent death, death due to infection, and meningitis or similar infections.

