Theoretical advantages of anterior decompression and fusion (ACDF) are the direct removal of the pain-generating disk fragment or osteophyte compression applied to the nerve root. Drawbacks are the approach-related complications, such as injury to neurovascular or other structures, and pseudoarthrosis, which may occur in a number of cases. The most feared acute complication is a postoperative hematoma, which, if untreated, may rapidly lead to airway obstruction or compression of the spinal cord. This occurs with an incidence of 1%. The incidences of other known complications with ACDF are as follows: esophagus lesion 0.25% [5], infection 0.1–1.6% [6], injury to the recurrent laryngeal nerve 0.6–2.9% [7], injury to the superior laryngeal nerve 0–1.25% [8], injury to the hypoglossal nerve 0–1.28% [9], vertebral artery injury 0.08% [10], dural tear 0.5–3.7% [11], spinal cord injury 0–0.24% [12], Horner’s syndrome 0.06% [13], brachial plexus injury 0.1% [14], C5 palsy 0–2.5% [15], and injury to the thoracic duct 0.08% [16].

Other complications associated with the anterior approach include intermittent early dysphagia which in most cases resolves [17]. In addition, adjacent segment disease (ASD) may occur, as spinal fusion has been blamed for increasing the incidence of degeneration in adjacent levels [18]. 25.6% will develop ASD within 10 years after ACDF and 7.5% will need further surgery. However, the cause for ASD is controversial, as disk degeneration is an age-related process affecting all disks and ASD may be a normal progression of the degenerative process affecting the disk adjacent to the fusion [19]. ACDF leads to clinical success in 83–91% of cases, with a reoperation incidence of 4–14% [20, 21].

Theoretical advantages with posterior foraminotomy (PF) include the following: fewer vital structures can be injured during the primary procedure and the segment is left unfused perhaps decreasing the risk for ASD. A disadvantage is that the decompression is indirect, meaning that the compressing fragment or the osteophyte is not removed, but the nerve root is allowed to move away from it, as the “roof” of the foramen is opened.

Approach-related complications with PF are postoperative hematoma, which may compress the spinal cord, and C5 palsy [15], where the exact pathophysiology is not fully understood.

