## Discussion

ACDF and PF are two common techniques for treating cervical radiculopathy. Both methods seem to result in a high frequency of clinical success with low incidences of complications and reoperations according to retrospective data, but at different costs as no implants are utilized in PF [37]. In an observational registry study, we did not find any difference between the two methods in terms of clinical outcome, complications, and reoperations [34]. As there may be undetected selection bias and underreporting of complications in a registry study, the results need to be confirmed in studies with higher level of evidence.

In most instances, a root canal stenosis is caused by osteophyte formation from the uncinate process and/or disk protrusion compressing the root from the anterior. The most determining factor for clinical success seems to be how well the nerve root is decompressed. A recent systematic review and meta-analysis of minimally invasive PF showed that arm pain improvement was greater in the PF group compared to the ACDF group, thus supporting the hypothesis of sufficient decompression with PF [55]. In ACDF, the compressing elements can be removed directly, whereas in PF, the decompression is indirect; by removing the “roof” of the root canal, the nerve root is allowed to move away from the compressing elements. Thus, the mode of decompression is fundamentally different between the two methods.

The level of decompression that is shown in retrospective series seems to be sufficient for both methods, i.e., to the range of 90% or more. However, PF shows larger variation in clinical success with range of 64–96% [35–37] and ACDF 83–91% [20, 21]; the reason for this variation is not exactly clear.

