The issue with restenosis at the index level of surgery and the need for re-decompression of the same nerve-root is another issue that needs more elaborate study. We know from prior studies that non-specified reoperation rates are in the range of 4–7% in PF and 4–14% in ACDF. We think that these data are not comparable and that the reasons for reoperation on index level are different. For PF, it will be the issues of inadequate decompression, but for ACDF, it will be inadequate decompression, hardware failure, and/or fusion problems, e.g., loosening or pseudoarthrosis. We believe that PF may in the long term have unremitting degeneration issues and that the risk for restenosis will increase over time. The reason may be the partial facetectomy in a loadbearing joint, in which the degeneration will continue [34].

The main question of this study is to evaluate if there is equal outcome between the two methods. Other questions are if complications and reoperations differ. We chose NDI as the primary outcome measure. The instrument has been used in multiple previous studies on cervical radiculopathy and focus on the pain and dysfunction associated with radiculopathy, i.e., is disease specific and allows comparison to previous work. We also include VAS separately for arm and neck pain as we believe this possibly separates the success of decompression from the morbidity associated with the different approaches. The EQ-5D was included as this is a non-disease specific quality-of-life instrument allowing comparison to other ailments.

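### Complications are reported by the unblinded operating surgeon, with no scheduled enquiry described, although possible under-reporting of complications is one stated reason for the trial

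*Protocol article*

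**What the plan says.** Why the trial is needed. The Discussion describes a registry study by the same group that found no difference in clinical outcome, complications or reoperations, and continues: "As there may be undetected selection bias and underreporting of complications in a registry study, the results need to be confirmed". Objectives {7} makes complications and secondary surgeries the tertiary variables, and the Discussion adds: "Other questions are if complications and reoperations differ".

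How events are to be found. Under Tertiary variables: "Tertiary variables, complications, and reoperations will be collected as they may occur". Under Adverse event reporting and harms {22}: "AE are reported by the senior spine surgeon that performed the surgical intervention to the primary investigator". For serious events, "they are reported by the senior spine surgeon according to the Swedish healthcare standards which depend on the type of SAE". Who will be blinded {17a} says that neither patient nor surgeon is blinded.

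What is scheduled. The assessment rows of the participant timeline {13} are imaging, NDI/NRS/EQ-5D and a postoperative CT. Plans for assessment and collection of outcomes {18a} has the questionnaires mailed at all four follow-up points. The section on the data monitoring committee {21a} describes weekly monitoring of questionnaires and radiology. Auditing {23} gives an independent observer the task of analysing adverse events.

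What is expected. The Background says: "Other complications associated with the anterior approach include intermittent early dysphagia which in most cases resolves". Section {22} lists: "Adverse events (AE) that are anticipated are infection, implant failure, neurologic impairment post-surgery, and other rare approach-related complications like esophagus perforation and nerve injury". Dysphagia is not named there.

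**The concern.** Randomisation answers the selection-bias half of the authors' criticism of their registry study. Nothing in the article answers the under-reporting half. The one stated reporting route depends on the person who operated, who knows the allocation. The article describes no scheduled contact after surgery at which that person would ask about, or be told of, a symptom.

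The events most easily lost are those that patients feel, that resolve, and that leave no trace on a scan. Early dysphagia after the anterior approach is the article's own example. If such events are lost at different rates in the two arms, the complications comparison is distorted. If they are lost at the same rate, the ratio survives but the absolute difference and the power shrink. Either way the doubt raised about the registry is only partly resolved.

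**Working it through.** **1. The plan's own figure.** Sample size {14} uses a difference of 15, SD 25, two-sided 5% and 80% power: n = 2 × (1.960 + 0.842)² × (25/15)² = 2 × 7.85 × 2.78 = 43.6, so 44 per group, as stated. The total of 110 against 88 evaluable implies a 20% allowance (1 − 88/110). This concerns the NDI. The article gives no sample-size or power figure for complications or reoperations, so what follows uses 110/2 = 55 per arm.

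**2. Could each described source find a transient symptom?**
- Operating surgeon {22}: yes, if told. No scheduled occasion for this is described.
- Mailed NDI/NRS/EQ-5D {18a, timeline}: the NDI content listed under Primary variable (daily activities, pain, headache, concentration) does not include swallowing or voice. NRS covers arm and neck pain. EQ-5D is called a general, non-specific instrument.
- Imaging (postoperative, 1 and 2 years): it would not record a symptom that has resolved.
- Weekly monitoring {21a}: described for questionnaires and radiology.
- Independent observer {23}: analyses events, with no stated means of detecting unreported ones.

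**3. Reoperations expected.** The Discussion quotes 4–7% (PF) and 4–14% (ACDF). If these apply over 2 years:
- PF: 55 × 0.04 = 2.2 to 55 × 0.07 = 3.9.
- ACDF: 55 × 0.04 = 2.2 to 55 × 0.14 = 7.7.

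**4. Effect of one or two missed reoperations on the crude ACDF:PF ratio.**
- Upper ends: 7.7/3.85 = 2.0. Two missed after ACDF: 5.7/3.85 = 1.5. Two missed after PF: 7.7/1.85 = 4.2.
- Lower ends: 2.2/2.2 = 1.0. One missed after ACDF: 1.2/2.2 = 0.55. One missed after PF: 2.2/1.2 = 1.8.

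**5. Effect of incomplete capture.** Observed rate = true rate × share captured. The documents give no capture shares, so these are assumptions.
- Equal true complication rates, with 90% captured in one arm and 60% in the other: observed risk ratio 0.9/0.6 = 1.5, or 0.67 the other way round. At true rates of 5%, 10% and 15% the false risk difference is 0.3 × rate = 1.5, 3.0 and 4.5 percentage points, or 0.8, 1.7 and 2.5 events in 55.
- Reoperation at 14% against 4%, with 70% captured in both arms: the ratio stays at 3.5, the difference falls from 10 to 7 points, and power falls from about 45% to 33%.
- The same true rates with unequal capture: the ratio becomes (0.14 × 0.6)/(0.04 × 0.9) = 2.3 with 60% captured after ACDF and 90% after PF, and (0.14 × 0.9)/(0.04 × 0.6) = 5.3 the other way round.

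**The case against.** The best defence has five parts.

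- **The surgeon may not be the only source.** Tertiary variables names no source, and section {18a} uses the Swedish Spine Register for data gathering. The authors' registry study compared complications, so the register may carry them. This stands in part. A reader might infer that a complication enters the trial only if the surgeon volunteers it, but the article says reported and does not make that route exclusive. Nor does it say that the register's follow-up forms ask about complications. The full protocol may add a complication form. Even so, the article itself states the reporter, the manner of collection and the assessment schedule, so the point rests on what is written.
- **Reoperations are hard events.** X-ray, MRI and CT at 1 and 2 years, read by two surgeons, should show many fusions, implant revisions or further decompressions, wherever they were done. This stands. A reader might infer that reoperations suffer from the same weakness as complications, but the Discussion's under-reporting remark concerns complications only. The residual risk is surgery at another hospital, together with patients excluded for non-response {18b} in an available-case analysis {20a}.
- **The direction is unknown.** A reader might infer that harm after ACDF is the harm being hidden. The documents do not support this. The list of anticipated events is open-ended and includes implant failure and esophagus perforation, and the authors expect more complications with the anterior approach. Both could raise reporting in that arm.
- **These are tertiary outcomes with little power anyway.** At 55 per arm, power is about 45% for 14% against 4% and 22% for 14% against 7%, even with complete capture. This stands. It limits what the comparison can show, but it also means that each event counts.
- **Patients are unblinded too.** Self-report would not remove reporting bias. This stands, and it limits what the remedy can claim.

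**Conclusion.** The point holds for complications. The plan names under-reporting as one of two possible weaknesses of the earlier evidence, then describes event-driven reporting by the unblinded operating surgeon and a follow-up schedule with no complication enquiry. The independent observer is a real safeguard, but on the described arrangements can work only on what has been reported.

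For reoperations it is a smaller, residual risk. It matters because only about 2–8 (ACDF) and 2–4 (PF) events are expected, assuming 55 per arm and that the quoted rates apply over 2 years.

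The size and direction of any imbalance between arms are not documented. The ratios of 1.5 and 0.67 illustrate assumed capture shares and are not an estimate. It would also go too far to say that the trial cannot confirm or refute the registry finding. Its main objective is the 2-year patient-reported outcome, randomisation deals with selection bias, and the primary NDI comparison is not touched by this point. This is a cheap improvement to a tertiary outcome.

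**What to change.** - Add one fixed patient-reported page, identical in both arms, to the questionnaires mailed at 4–6 weeks, 3 months, 1 year and 2 years. Ask about swallowing, voice, new weakness, wound problems, and any further neck surgery with its date and place.
- Add the page as an assessment row in the participant timeline {13}.
- Keep surgeon reporting as a second source.
- Use confirmed dates of reported surgery in the time-to-revision analysis in Statistical methods {20a}.
- Name dysphagia among the anticipated events in section {22}.

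Costs: a longer questionnaire, its data entry, and more minor events on record. The change would probably need resubmission to the ethics authority under section {25}, which covers changes to outcome measures. Recruitment began in January 2020 (Trial status), so patients already past the early time points would have no early data. The page will not reach patients who do not answer the mailings; for them, surgeon reports and any imaging obtained remain the described sources. Completeness should improve, but bias from unblinded reporting will not be removed.
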